Previous research by our team has demonstrated that applying specific mode electroacupuncture stimulation (SMES) to the GV20 (Baihui) and GV26 (Shuigou) acupuncture points could open the BBB in rats (8). Through a series of studies, we have determined that the optimal parameters for SMES are 2/100 Hz, 3 mA, 6 s on and 6 s off (6–6 s), with a total stimulation duration of 40 min (8–10). Further research revealed that the effect of SMES on opening the BBB exhibits a time window, is dependent on the duration of stimulation, and is reversible (9, 11). Moreover, SMES-induced BBB opening does not cause adverse effects such as cerebral edema, glial cell activation, or neuronal apoptosis (9). The SMES applied at GV20 and GV26 acupoints has been shown to decrease the expression of tight junction proteins ZO-1 and occludin within the BBB, which can explain part of the potential mechanism of SMES opening the BBB (12). Additionally, SMES can induce NGF to cross the BBB, thereby improving motor and cognitive functions in rats during the recovery phase of middle cerebral artery occlusion/reperfusion (MCAO/R) (12). Another randomized controlled trial by our team, which is awaiting publication, investigating SMES combined with NGF for ischemic stroke, has shown significant therapeutic efficacy on motor and cognitive function and good safety (13).

These studies further consolidate our central hypothesis that the application of SMES to open the BBB will facilitate the delivery of exogenous NGF to achieve effective concentrations within the injured brain of post-stroke patients. We hypothesize that this approach can also benefit patients with PSD. Our team plans to conduct a pilot randomized controlled clinical trial on the treatment of dysphagia after ischemic stroke using SMES combined with NGF, to assess its effectiveness and safety.

To separately test the “BBB-opening carrier effect” of SMES, the “neuro-reparative effect” of NGF, their potential synergistic interaction, and to control for the non-specific effects of needling at the GV20 and GV26 acupoints themselves, we have adopted a 2 (SMES/Acupuncture) × 2 (NGF/Placebo) factorial, double-dummy design. This design aims to isolate and quantify the independent and combined contributions of each intervention component, providing a foundation for future mechanistic exploration and treatment optimization.

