### Outcomes

#### Primary outcome

The primary outcome is the Functional Oral Intake Scale (FOIS) (20), which reflects the overall intake capability based on swallowing function. The FOIS is a 7-point ordinal scale with a score range of 1–7. Oral intake ability is measured in terms of intake method and food type. Higher scores indicate better oral intake ability. Assessment time frames: at baseline; at week 2, 4, 6, and 12. Week 6 post-intervention is the primary endpoint.

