### Statistical analysis

The overall dropout rate and the dropout rate due to adverse events will be calculated for each group. It will be statistically determined whether each group received the treatment as specified in the study protocol in terms of duration and number of sessions, and the number and percentage of subjects with compliance < 80% will be calculated. Efficacy analysis will be performed in the full analysis set. Participants who have been randomized and have received at least one treatment session will be included in the full analysis set (FAS). All hypothesis tests will be two-sided, and *p*-value < 0.05 will be considered to indicate statistical significance of the tested difference. For ordinal outcomes (FOIS, DOSS, PAS, and mRS), non-parametric tests (Kruskal–Wallis *H* test for group comparisons, with post-hoc Mann–Whitney *U* tests and alpha adjustment) will be used for cross-sectional analyses. For longitudinal ordinal outcomes, generalized estimating equations (GEE) with an appropriate link function (e.g., logit) and working correlation matrix will be the primary method for analyzing these outcomes across multiple time points (FOIS, mRS). The normality of continuous data (MBI, fNIRS metrics) will be assessed using the Shapiro–Wilk test. Provided that parametric assumptions are met, (repeated-measures) ANOVA will be applied. Should the assumptions be violated, non-parametric alternatives (e.g., Kruskal–Wallis test, Friedman test) will be used. The study results will include three-factor (EA factor/NGF factor/time factor) repeated-measure data, with measurement data analyzed using three-factor repeated-measures analysis of variance and ordinal data analyzed using the generalized estimating equation (GEE) to test for differences. The Bonferroni method will be used to adjust for the significance of multiple comparisons.

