Multimodal findings from clinical, electrophysiological, and imaging studies suggest that dysphagia recovery after stroke involves neuroplastic changes in the contralesional hemisphere across sensory, motor, and white matter domains (31–39). This body of evidence supports a compensatory model of contralesional neuroplasticity as the driving mechanism for recovery (1). fNIRS and electroencephalography (EEG) are two convenient brain function imaging techniques that have attracted significant attention in recent years and have yielded numerous significant findings on the mechanism of acupuncture’s effects on the brain (14, 40–42). Currently, the application of EEG in the study of PSD remains limited, but many fNIRS studies have proved that the effect of acupuncture can upregulate activation patterns in the cortical swallowing network and strengthen functional integration among specific regions (14). This study is not focused on the direct cerebral effects of acupuncture. Instead, fNIRS was chosen as the research method to examine the swallowing network recovery induced by NGF. In terms of study design, the four-arm study can highlight the interaction effect between SMES and NGF, and distinguish it from the independent effect of acupuncture at the GV20 and GV26 acupoints.

In China, a significant proportion of PSD patients have prior acupuncture experience, making patient blinding challenging (43). Thus, conventional acupuncture rather than sham acupuncture will serve as the control to optimize blinding feasibility.

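### Week-6 FOIS, the primary endpoint, is not tied to an analysis that estimates the SMES, NGF and interaction effects the 2×2 design is meant to measure

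*Protocol article*

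**What the plan says.** - **Design and aim.** The Introduction adopts a "2 (SMES/Acupuncture) × 2 (NGF/Placebo) factorial, double-dummy design" and adds: "This design aims to isolate and quantify the independent and combined contributions of each intervention component". The Discussion repeats that "the four-arm study can highlight the interaction effect between SMES and NGF".
- **Endpoint.** The Primary outcome section schedules FOIS at five visits ("Assessment time frames: at baseline; at week 2, 4, 6, and 12") and singles out one of them: "Week 6 post-intervention is the primary endpoint".
- **Method A.** In the Statistical analysis section, FOIS heads the list of ordinal outcomes for which a Kruskal–Wallis test with post-hoc Mann–Whitney U "tests and alpha adjustment) will be used for cross-sectional analyses".
- **Method B.** The next sentence says that GEE "will be the primary method for analyzing these outcomes across multiple time points (FOIS, mRS"). A later sentence gives the repeated-measures data three factors (EA, NGF, time) and again assigns GEE to ordinal data.
- **Multiplicity.** Bonferroni is named, without a list or count of comparisons.

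**The concern.** A comparison of arms on one scale at one visit is a cross-sectional analysis. On the literal text the primary endpoint therefore goes to Method A, because Method B is primary only for analysis over several visits. Method A does not produce the quantities that the factorial layout was chosen to provide. Method B can produce them, but the plan does not say that the deciding result is a week-6 contrast, or which term of the model it is.

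What is at stake is what counts as the primary result. If this stays open until the data are seen, the choice between an omnibus rank test, a pairwise test, a pooled GEE term and a week-6 GEE contrast could follow the results. A significant Kruskal–Wallis test could also be taken as support for synergy, which it does not address.

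**Working it through.** **1. The plan's own figure.** The Sample size section gives at least 30 per group and 20% dropout. 30 × (1 + 0.20) = 36 per group and 4 × 36 = 144, as stated. After 20% dropout, 36 × 0.8 = 28.8 remain, so about 29 to 30 per arm are evaluable; 30 is used below. The document gives no effect size, SD or power, so every effect size here is an assumption.

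**2. What each method tests.** Write μ00 for acupuncture + placebo, μ01 for acupuncture + NGF, μ10 for EA + placebo and μ11 for EA + NGF.

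- SMES main effect: ½[(μ10 − μ00) + (μ11 − μ01)]
- NGF main effect: ½[(μ01 − μ00) + (μ11 − μ10)]
- Interaction: (μ11 − μ01) − (μ10 − μ00)
- Kruskal–Wallis: a 3-df test that all four distributions are the same. It estimates none of the three.
- Mann–Whitney pairs: four of the six possible pairs are simple effects, such as SMES given NGF (μ11 against μ01). No pair is an average of two simple effects or their difference.
- GEE term pooled over visits: if the four post-baseline visits are weighted equally (an assumption), week 6 carries one quarter of the weight. Week 12, six weeks after treatment ends, carries as much.

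**3. Does a Kruskal–Wallis result inform the interaction?** Simulation: 4,000 trials per row, 30 per arm, a latent normal variable cut into 7 levels. A 2×2 linear model on the scores stands in for the factorial analysis.

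| Assumed truth | Kruskal–Wallis rejects | SMES main effect rejects | Interaction rejects |
|---|---|---|---|
| SMES 0.6 SD and NGF 0.6 SD, additive | 96% | 85% | 6% |
| 0.8 SD in EA + NGF only | 85% | 51% | 52% |
| SMES 0.5 SD only | 57% | 74% | 6% |

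Kruskal–Wallis rejects often in the first two rows, yet there is no interaction in the first and a large one in the second. In the third row it has less power than the main-effect test for the effect that is present.

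**4. Power of week-6 factorial contrasts.** With n per arm, SE(main) = SD × √(1/n) and SE(interaction) = SD × √(4/n). For n = 30 these are 0.183 SD and 0.365 SD. Power ≈ Φ(δ/SE − 1.96) at two-sided 5%, without baseline adjustment:

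| δ (SD) | Main effect | Interaction |
|---|---|---|
| 0.4 | 59% | 19% |
| 0.5 | 78% | 28% |
| 0.6 | 91% | 38% |
| 0.8 | 99% | 59% |

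If all three contrasts form the Bonferroni family, the threshold is 0.05/3 = 0.0167 (z = 2.394). At δ = 0.6 the main effect then has Φ(3.286 − 2.394) = 81% and the interaction Φ(1.643 − 2.394) = 23%.

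**The case against.** The strongest reply is that the plan already contains the factorial analysis. FOIS is ordinal with repeated visits, GEE is called the primary method with FOIS named, and the three-factor sentence supplies EA, NGF and time. On that reading Kruskal–Wallis is for DOSS and PAS, which have week 6 as their only post-baseline visit, and the open question is just which GEE contrast is primary, a detail an SAP could settle. Part of this stands: a reader might infer that the plan has no factorial analysis of FOIS, and that would be wrong. But FOIS is itself listed under the cross-sectional method, and the primacy of GEE is limited to several visits while the endpoint is one visit. The article states two methods for one endpoint; it does not merely leave a detail out.

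It is also fair that the pairwise tests are informative about simple effects, and that this is a pilot. Yet the Sample size section gives effectiveness as an aim, and the analysis section sets a 5% significance threshold.

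Several stronger readings are tempting but not supported:

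- **Bonferroni over six pairs.** The plan gives no number of comparisons.
- **Week 12 as the primary visit.** The endpoint wording could be parsed as six weeks after treatment. Beside a visit list that separates weeks 6 and 12, and a 6-week treatment, it plainly means the end of treatment.
- **A large power loss from rank tests as such.** With 0.6 SD in EA + NGF only, 29 per arm and an assumed baseline correlation of 0.6, a Kruskal–Wallis-gated Mann–Whitney test at 0.05/6 has about 27% power and a baseline-adjusted contrast at 5% about 74%. A plain Mann–Whitney test at 5% has 57%, and the adjusted contrast at 0.05/6 has 44%. The gap comes mainly from the assumed six-way split and the baseline adjustment.
- **Serious false-positive inflation.** Counting either of two tests as a success gave roughly 6% to 8% under the null with a linear proxy for GEE. That is modest, and the plan does not say that either may be claimed.

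**Conclusion.** The concern holds in this form: the plan names two methods for FOIS, and neither is tied to a factorial contrast at week 6. On the literal reading, the method that covers a single visit cannot estimate the SMES main effect, the NGF main effect or their interaction. This is structural and needs no assumed effect size.

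The numerical illustrations do rest on assumptions: about 30 evaluable per arm, effects of 0.4 to 0.8 SD, a 7-level score, and a linear model in place of the ordinal GEE. They show that a Kruskal–Wallis rejection does not separate additive from synergistic effects. They also show that the interaction, which the plan puts forward as a target, would have only about 19% to 59% power even with the right contrast. The finding does not extend to an absent factorial model, a stated six-pair adjustment or an ambiguous visit.

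**What to change.** In the Statistical analysis section:

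1. Make the three-factor ordinal GEE (EA, NGF, time and their interactions), with baseline FOIS as a covariate, the sole primary analysis of week-6 FOIS.
2. Take the EA, NGF and EA×NGF contrasts at week 6 (end of treatment) from that model, name which one is primary, and report each with a 95% CI.
3. Label Kruskal–Wallis and Mann–Whitney tests of FOIS as supportive.
4. State the family of week-6 contrasts to which the Bonferroni adjustment applies.

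The change is to wording only, needs no new data, and should be made before unblinding. Its cost is that other pairwise comparisons become descriptive. It also does not cure the low interaction power: roughly 38% for an assumed 0.6 SD at 30 per arm without baseline adjustment, and about 23% if all three contrasts share the 5%. The report should therefore rest on the interval for the interaction, and a non-significant interaction should not be read as evidence that there is none.

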#### Secondary outcomes

Secondary outcomes will include the following:

The Dysphagia Outcome and Severity Scale (DOSS): The DOSS integrates swallowing efficiency and safety. The DOSS scores range from 1 to 7 with 7 grades, and lower scores indicate more severe dysphagia (21). Assessment time frames: at baseline; at week 6.

The Penetration Aspiration Scale (PAS): The PAS focuses on the safety of swallowing. The PAS scores range from 1 to 8 with 8 grades, and higher scores indicate higher risk of penetration and aspiration (22). Assessment time frames: at baseline; at week 6.

The Modified Rankin Scale (mRS): The mRS is a valid and clinically relevant instrument for assessing recovery from stroke (23), and the mRS scores range from 0 to 5 with 6 grades. Assessment time frames: at baseline; at week 2, 4, 6.

The Modified Barthel Index (MBI): The MBI (24) is a common scale for evaluating activities of daily living (ADL), with a total score of 100 points. Assessment time frames: at baseline; at week 2, 4, 6.

Oxygenated hemoglobin and deoxygenated hemoglobin in cerebral cortex: An fNIRS device with wavelengths of 730 and 850 nm (Danyang Hui Chuang Medical Equipment Co., Ltd.) will be used to detect changes in HbO2 and HbR in swallowing-related brain areas during rest and voluntary swallowing. A total of 35 channels will be distributed across the right and left prefrontal cortices (RPFC/LPFC), motor areas (RM1/LM1), somatosensory areas (RS1/LS1), and pre-motor and supplementary motor areas (RPM/LPM). The sampling rate of the fNIRS system will be set to 11 Hz. According to the anatomical positions defined by the international 10–20 system, the probes will be placed on the scalp surface of the subjects based on four reference points (nasal root, external occipital protuberance, left pre-auricular point, right pre-auricular point). A schematic diagram of the probe and channel arrangement is shown in Figure 4 (14). Participants will be seated in a quiet fNIRS assessment room to reduce the impact of noise.

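### The example non-parametric fallbacks for MBI and fNIRS cannot test the SMES×NGF interaction, and they conflict with the unconditional three-factor ANOVA in the same paragraph

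*Protocol article*

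**What the plan says.** All of this is in the Statistical analysis section of the protocol article unless another section is named.

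- **Gate:** "The normality of continuous data (MBI, fNIRS metrics) will be assessed using the Shapiro–Wilk test".
- **If assumptions hold:** "Provided that parametric assumptions are met, (repeated-measures) ANOVA will be applied".
- **If they do not:** "Should the assumptions be violated, non-parametric alternatives (e.g., Kruskal–Wallis test, Friedman test) will be used".
- **Next sentence, on the EA, NGF and time factors, with no condition attached:** "with measurement data analyzed using three-factor repeated-measures analysis of variance".
- **Follow-up tests:** for the ordinal outcomes only, the plan names "Kruskal–Wallis *H* test for group comparisons, with post-hoc Mann–Whitney *U* tests and alpha adjustment". It also says generally: "The Bonferroni method will be used to adjust for the significance of multiple comparisons".

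Under Secondary outcomes, the MBI "is a common scale for evaluating activities of daily living (ADL), with a total score of 100 points" and is measured at baseline and weeks 2, 4 and 6. The fNIRS measures are taken at baseline and week 6. The Introduction explains that the four arms form a 2×2 factorial meant to measure what SMES and NGF contribute separately and jointly. The Discussion again gives the SMES×NGF interaction as a reason for having four arms.

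**The concern.** A fallback should answer the same question as the analysis it replaces. Here the main analysis has three factors (EA, NGF and time), and the two tests offered in its place have one factor each. If the fallback is followed, the SMES×NGF interaction is no longer tested for MBI or fNIRS, and there is no estimate of any component's contribution.

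The plan is also ambiguous at the moment it matters. When normality is rejected, one sentence points to rank tests and the next to the three-factor ANOVA. Nothing says which governs. The choice would then be made with the trial's own data in view, between analyses that answer different questions.

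**Working it through.** The plan gives no figure of its own on this point. The check therefore sets the tests against the design's question and then illustrates the result by simulation.

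**1. What each test addresses.** Write μ(EA, NGF) for the arm means at a visit. The interaction is

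I = [μ(1,1) − μ(0,1)] − [μ(1,0) − μ(0,0)].

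| Analysis | Between-arm factor | Time | Tests I? | Effect estimate? |
|---|---|---|---|---|
| Three-factor repeated-measures ANOVA | EA, NGF, EA×NGF | yes | yes | yes |
| Kruskal–Wallis, four arms | one factor with four levels (3 df) | one visit | no | no |
| Kruskal–Wallis on a margin | EA or NGF, one at a time | one visit | no | no |
| Friedman | none | yes | no | no |

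For fNIRS, with two visits, Friedman reduces to a sign-type test of before against after.

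**2. Simulation inputs.** From the documents: 36 per arm (30 × 1.2 = 36) and the four MBI visits. Everything else is assumed, because the documents give no MBI effect size or spread:
- Errors are skewed (exponential), with a person-level component of SD 1 and a visit-level component of SD 0.7. The total SD at a visit is √(1 + 0.49) = 1.22.
- Effects grow linearly from zero at baseline to their full size at the last visit.
- There are 2,000 trials per scenario and no dropout, and tests are two-sided at 0.05.

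Last-visit arm means, in the order (EA+NGF, EA only, NGF only, neither), give these values of I:
- Common time trend only: 0.8, 0.8, 0.8, 0.8; I = 0.
- SMES effect 0.8 only: 1.6, 1.6, 0.8, 0.8; I = 0.
- Two additive effects of 0.5: 1.8, 1.3, 1.3, 0.8; I = 1.8 − 1.3 − 1.3 + 0.8 = 0.
- Synergy only: 1.6, 0.8, 0.8, 0.8; I = 0.8.
- Crossover with no average trend: 0.4, −0.4, −0.4, 0.4; I = 1.6.

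**3. Rejection rates.**

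| Scenario | True I | Friedman, all arms | Kruskal–Wallis, four arms | Kruskal–Wallis, EA margin | Kruskal–Wallis, NGF margin | 2×2 contrast on change |
|---|---|---|---|---|---|---|
| Time trend only | 0 | 100% | 4.8% | 4.8% | 3.6% | 5.4% |
| SMES only | 0 | 100% | 98.6% | 99.8% | 3.6% | 6.0% |
| Additive | 0 | 100% | 95.0% | 81.5% | 81.4% | 5.8% |
| Synergy only | 0.8 | 100% | 94.7% | 59.6% | 60.2% | 68.2% |
| Crossover | 1.6 | 3.3% | 97.8% | 3.7% | 4.0% | 99.6% |

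Friedman responds to the time trend and not to treatment. Four-arm Kruskal–Wallis shows that the arms differ, but rejects about equally often whether I is 0 (95.0%) or 0.8 (94.7%). Applying it to change from baseline does not help: 99.3% under additive effects and 98.2% under synergy. Only the factorial contrast follows I.

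**4. How often the fallback would be reached.** The document does not fix how Shapiro–Wilk is applied. With one test per arm and visit for MBI there are 4 × 4 = 16 tests. If these are independent and any rejection triggers the switch, normal data would trigger it with probability 1 − 0.95^16 = 0.56. Simulation with an assumed within-person correlation of 0.7 gives 55% at 29 per arm (36 × 0.8 = 28.8) and 52% at 36. A single test of pooled within-arm residuals would trigger it in about 5%. Normal data alone thus give a range of about 5% to 56%, and skewed or bounded scores would push it higher by an amount the document cannot settle.

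**The case against.** The strongest reply is that the paragraph is less damaging than it looks.

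- **The list is open.** The two tests are given as examples, so a factorial rank method is not excluded. That is true, but both examples lack the factorial structure, and no suitable method is named for MBI or fNIRS.
- **The next sentence keeps the factorial ANOVA.** This also stands: it is not established that the fallback replaces it. But the sentence does not resolve the matter, because it does not say that it prevails when assumptions fail. The complaint is therefore partly one of two adjacent sentences in conflict.
- **Detail belongs in the analysis plan.** A full plan may well settle how normality is tested. The gate and the fallback tests, however, are stated here.
- **Consequence is limited.** The primary outcome, FOIS, is ordinal and never enters this branch, and the trial calls itself a pilot. Both points stand.

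A reader might infer three stronger things that the document does not support. First, that the fallback leaves no way to examine SMES or NGF at all. Kruskal–Wallis is a valid comparison of randomised arms, and on a factor margin it detected an SMES effect in 99.8% of simulated trials, with the NGF margin at 3.6%. Main effects at a visit can be tested, though not estimated. Second, that Friedman would be run within each arm and the p-values compared across arms. That would be misleading under shared recovery, but no such comparison is planned. Third, that the switch is nearly certain. High rates can be produced for MBI by assuming bounded score shapes, but the document gives no distribution. For fNIRS connectivity, the Fisher transformation weakens any presumption of non-normality.

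**Conclusion.** The point holds in a limited form. The named fallbacks drop the EA×NGF×time structure, cannot test the SMES×NGF interaction or its course over time, and give no effect estimate. They also conflict with the unconditional three-factor ANOVA, which leaves the governing analysis open until the data are seen.

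That the tests cannot address the interaction follows from their construction and needs no assumption. The rejection rates are illustrations that rest on the assumed effect sizes, error shape and time trend. The probability of reaching the fallback cannot be stated from this document. The effect is confined to secondary outcomes (MBI and fNIRS). It should be corrected, but it does not threaten the primary analysis.

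**What to change.** Remove the normality-triggered switch and state one factorial model per outcome, kept whatever Shapiro–Wilk shows:

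- **MBI:** a repeated-measures or linear mixed model for weeks 2, 4 and 6, with EA, NGF, time and all their interactions, adjusted for baseline MBI.
- **fNIRS metrics:** the week-6 value modelled on EA, NGF and EA×NGF, adjusted for the baseline value.
- **Non-normality:** robust or participant-level bootstrap standard errors, with estimates and confidence intervals for the EA, NGF and interaction effects.
- **If a rank-based analysis is wanted:** a factorial one, such as the ANOVA-type statistic, as a sensitivity analysis. Friedman and Kruskal–Wallis should not replace the factorial model.

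The gate, the fallback and the three-factor sentence would then be merged into one statement, which removes the conflict. The cost is revised wording and slightly different code, with no extra data or participants. A smaller step would also remove the contradiction: one sentence saying that the EA×NGF×time model is retained whether or not normality holds.

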### Randomization and allocation concealment

One hundred forty-four eligible participants who have affirmed and signed informed consent will be randomly assigned in a ratio of 1:1:1:1 into the electroacupuncture (EA) + NGF group, the EA + placebo group, the acupuncture + NGF group or the acupuncture + placebo group, each with 36 participants, via a central randomization system, which is managed by a third-party mathematician outside the study and used to generate and conceal the allocation sequence. The randomization sequence will be generated in varying block sizes.

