### Statistical methods

#### Sample size

This pilot study aims to assess the effectiveness and safety of SMES combined with NGF for dysphagia after ischemic stroke and determine the feasibility of a further definitive trial. To ensure that the clinical trial data have sufficient statistical power, the minimum sample size of each group of subjects should not be less than 30 participants (27). To account for an anticipated 20% dropout rate, the sample size was inflated to 36 participants per group, resulting in a total enrollment of 144 participants.

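### Single-step Bonferroni is valid, but Holm's step-down procedure controls the same family-wise error with equal or greater power

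*Protocol article*

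**What the plan says.** The relevant text is in the protocol article, under Statistical analysis.

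- **Level.** "All hypothesis tests will be two-sided", and a p-value below 0.05 "will be considered to indicate statistical significance of the tested difference".
- **Ordinal outcomes (FOIS, DOSS, PAS, mRS), cross-sectional.** A Kruskal–Wallis test comes first, "with post-hoc Mann–Whitney *U* tests and alpha adjustment". The adjustment is not named at this point.
- **Repeated measures.** GEE is used for ordinal outcomes and three-factor (EA, NGF, time) repeated-measures ANOVA for measurement data.
- **General rule, closing the paragraph.** "The Bonferroni method will be used to adjust for the significance of multiple comparisons".

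The number of comparisons in a family is not stated. Neither is a reason for the single-step form, and no simultaneous confidence intervals are mentioned. Participants "will be randomly assigned in a ratio of 1:1:1:1", "each with 36 participants". The sample size section rests on a cited rule that "the minimum sample size of each group of subjects should not be less than 30 participants", with no effect size or target power.

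**The concern.** Bonferroni tests every member of a family of m hypotheses at 0.05/m, however many have already been rejected. Holm starts at the same level and relaxes it after each rejection, with the same guarantee on the family-wise error. If simultaneous confidence intervals are not wanted, nothing is gained by staying with the single-step form.

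Power is at stake for the second and later comparisons. The trial has four arms, a minimum group size not derived from any effect, and an introduction that asks for the separate and combined contributions of SMES and NGF. More than one comparison is therefore of interest.

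**Working it through.** **Inputs from the article.** Four arms; two-sided 0.05; 30 per arm as the stated minimum and 36 per arm randomised (30 × 1.20 = 36, which reproduces the article's figure); FOIS with 7 ordered levels. The article gives no power figure to reproduce.

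**Assumptions.** All six arm pairs form the family (4 × 3 / 2 = 6). The seven levels are equally likely in a reference arm. Effects are shifts on a latent normal scale.

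**Why Holm is never worse.** Order the p-values and compare the j-th smallest with 0.05/(m − j + 1), stopping at the first failure. Suppose m0 nulls are true. The first true null to be rejected is reached at step j ≤ m − m0 + 1, where the threshold is at most 0.05/m0. The chance that any of the m0 true nulls falls below 0.05/m0 is at most m0 × 0.05/m0 = 0.05, with no independence needed. Every Holm threshold is at least 0.05/m, so Holm rejects whatever Bonferroni rejects.

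**Thresholds for m = 6.**

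| Step | Bonferroni | Holm | Shaffer after a significant omnibus test |
|---|---|---|---|
| 1 | 0.0083 | 0.0083 | 0.0167 |
| 2 | 0.0083 | 0.0100 | 0.0167 |
| 3 | 0.0083 | 0.0125 | 0.0167 |
| 4 | 0.0083 | 0.0167 | 0.0167 |
| 5 | 0.0083 | 0.0250 | 0.0250 |
| 6 | 0.0083 | 0.0500 | 0.0500 |

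The last column uses divisors 3, 3, 3, 3, 2, 1. If four distributions are not all equal, the arms split as 3+1 (three true pairwise nulls), 2+2 (two), 2+1+1 (one) or all different (none). At most three nulls can therefore still be true once the omnibus null is false. If all four are equal, the omnibus test at 0.05 controls the error.

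**Simulation.** 20,000 trials per scenario, with tie-corrected Mann–Whitney tests on all six pairs. The Bonferroni and Holm columns carry no Kruskal–Wallis gate; the Shaffer column does. Only the combination arm is shifted, by 0.75 SD.

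| | Bonferroni | Holm | Omnibus + Shaffer |
|---|---|---|---|
| 30 per arm: average power per true difference | 50.5% | 53.5% | 59.4% |
| 30 per arm: at least one rejection | 75.8% | 75.8% | 79.4% |
| 36 per arm: average power per true difference | 61.9% | 65.1% | 70.4% |
| 36 per arm: at least one rejection | 85.1% | 85.1% | 87.8% |

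The gate matters little: at 36 per arm, the gated averages for Bonferroni and Holm are 61.7% and 64.9%. Across scenarios it blocked a Bonferroni rejection in at most 0.8% of trials.

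**Other effect patterns, average power** (shifts in SD; two arms with a single active component, combination arm last):

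- (0, 0.5, 0.5, 1.0), 30 per arm: 31.2%, 34.1%, 38.0%.
- (0, 0.35, 0.35, 1.0), 36 per arm: 39.9%, 43.3%, 46.8%.
- (0, 0, 0, 1.0), 36 per arm: 89.3%, 91.5%, 93.4%.

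Holm's gain in average power was about 2 to 5 points over all scenarios. The family-wise error never exceeded 0.05; the maxima were 0.039 for Bonferroni, 0.039 for Holm and 0.046 for omnibus plus Shaffer.

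**The case against.** **Bonferroni is prespecified, valid and conservative, and the trial calls itself a pilot.** This stands. The article makes no error here, and a sponsor who keeps Bonferroni keeps a sound error rate.

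**The six-pair family is assumed.** This also stands for the size of the gain. If only the three contrasts of the combination with the other arms were tested, Bonferroni would already use 0.05/3 = 0.0167, which is Shaffer's first threshold. In a separate run (3,000 trials, 30 per arm, combination arm better by an assumed cumulative odds ratio of 4.5), the power to win all three was 57.8% with Bonferroni on three contrasts and 57.9% with omnibus plus Shaffer on six pairs. Shaffer's advantage there is thus largely a matter of family size. Holm's dominance does not depend on the choice of family.

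**A reader might infer a larger loss from the claim that the combination beats each of the other three arms.** At 30 per arm and 0.75 SD, power for all three rises from 24.9% with Bonferroni to 30.7% with Holm and 35.5% with omnibus plus Shaffer. The article does not make that joint claim a success criterion. If it did, the claim would be an intersection-union test: all three must be rejected, so each could be tested at 0.05 with no adjustment. These figures are no measure of harm to this trial.

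**A reader might also infer that Shaffer's procedure should replace Bonferroni throughout.** The text does not support that. The article's rule is general, and Shaffer's divisors do not carry over to the factorial effects or to comparisons across time points. They also require the pairwise nulls to be equal distributions. If the Mann–Whitney null is read as a probability of one half, the nulls are not transitive and the at-most-three argument fails.

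**Conclusion.** The point holds as an optional efficiency improvement. That Holm is at least as powerful as Bonferroni at the same family-wise error needs no assumption about effects, dependence or family, beyond the family having at least two members. The size of the gain does need assumptions. With six pairs and one arm shifted by 0.75 SD, it is 53.5 − 50.5 = 3.0 points of average power at 30 per arm and 65.1 − 61.9 = 3.2 points at 36 per arm. Holm does nothing for the smallest p-value, so the chance of at least one finding is unchanged. The further gain from Shaffer (59.4 − 53.5 = 5.9 points at 30 per arm) is confined to the all-pairs setting after a significant Kruskal–Wallis test.

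**What to change.** Replace the Bonferroni sentence with one of equal scope, for example: *Within each family of comparisons (pairwise, factorial, time-point and fNIRS), p-values will be adjusted by Holm's step-down method.* Use the same name where the post-hoc Mann–Whitney tests now refer only to an alpha adjustment.

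Optionally add that Shaffer's divisors 3, 3, 3, 3, 2, 1 will be used where all six arm pairs are tested after a significant Kruskal–Wallis test, with equality of distributions as the null. A sentence restricted to pairwise tests should not replace the general one, because the other comparisons would then have no stated rule.

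The change costs one sentence, made before unblinding, and no extra participants. Step-down methods do not give the simple simultaneous confidence intervals that Bonferroni gives. The article plans none, and unadjusted 95% intervals can be reported beside the adjusted p-values.
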